#### Sham tDCS condition

The sham tDCS intervention will follow the same procedure as the active conditions, even though placebo current stimulation will be applied. At the beginning of the session, during the first 30 secs, electrical current will be ramped up emulating the ipsi-DLPFC + contra-CEREB stimulation condition. Immediately thereafter, a 5-secs ramp-down will cease the delivery  of electrical current. During the following 20 min of the session no electrical current will be administered. At the end of the session, the same procedure will be repeated, delivering a 5-secs ramp up followed by a 30-secs ramp down to null intensity. This protocol commonly known as “FISSFO” (Fade In of Stimulation, brief real Stimulation, Fade Out) has been extensively used in clinical trials to mimic during sham conditions the tingling and itching skin sensations perceived during the ramp up and ramp down of tDCS intensity [45]. In the current clinical trial, patients will undergo tDCS treatment during the late subacute to chronic phase following a stroke, hence optimal for non-invasive neuromodulation, but during which, instances of spontaneous recovery might still operate. Moreover, for ethical reasons, while participating in our study, patients will continue their conventional physical rehabilitation program (see next section for details), which *per se* could also contribute recovery. In such circumstances, and also to counter improvement effects caused by familiarization and training in evaluation tasks performed several times during the study follow-up, a sham stimulation group is key to identify genuine recovery fostered by transcranial stimulation.

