#### Associated clinical rehabilitation

In order not to undermine optimal recovery potential and since we are testing an innovative tDCS protocol for which clinical efficacy is not warranted, all participants will be enrolled in parallel, in a similar “live” on-site rehabilitation program. Stimulation sessions will be conducted in the morning (8–12 am) and “live” rehabilitation sessions delivered independently in the same institution will follow. Rehabilitation activities during participation in the trial aim to maximize the chances of optimal recovery given the uncertain therapeutic value of our intervention and were specifically requested by our local Institutional Review Board for ethical reasons.

The on-site “live” program is based on an intense multidisciplinary rehabilitation plan encompassing specific goal-directed qualitative interventions, combining physical therapy, occupational therapy, neuropsychological, and speech therapy interventions, with a duration and periodicity of 1 to 2.5 hours a day, 2–3 days a week. Hence, all participants will conduct equivalent rehabilitation activities based on identical goal-directed qualitative occupational principles. On stimulation days, when hospital rehabilitation cannot be performed live on-site, participants will be instructed to carry out 1–2 hours of rehabilitation at home based on the same activities usually performed in the hospital. Clinical physical therapy is mainly focused on gross motor functions and postural control training (i.e., reaching, straightening, and support abilities), somatosensory integration, and gait rehabilitation. Occupational therapy exercise upper limb fine motor function, spasticity reduction, manual skill training, and multisensory stimulation. Finally, neuropsychological rehabilitation is mainly centered on training executive function and the management of emotions (i.e., impulsivity, liability, childish behavior, apathy, orientation and depression).

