## Data analyses

### Analysis of clinical and cognitive performance outcome measures

Outcomes extracted from computer-based tasks and clinical scores (see the previous section) will be analyzed to explore the differential ability of active tDCS conditions compared to sham stimulation to induce upper limb motor recovery following a stroke. For the clinical tests (FMA, NIHSS, MoCA, and hemispatial neglect tests), mean group scores post vs. pre-tDCS baseline intervention,and during the follow-up assessment, will be compared across experimental groups. Sociodemographic data will also be compared between treatment groups (Group 1: ipsi-DLPFC, Group 2: contra-CEREB, Group 3: ipsi-DLPFC + contra-CEREB, Group 4: SHAM) to identify potential collapse factors.

In order to quantify changes in motor performance with the visuo-motor adaptation task,and assess tDCS effects applied over the cerebellum or the dorsolateral prefrontal areas on upper limb voluntary motion, the following set of measures will be used: (i) the angular trajectory error (“SumErr”; cm) estimating accuracy, consisting of the sum of observed deviations from the ideal linear trajectory at peak tangential velocity (PV)for each trial of the motor adaptation block; (ii) the area under the learning curve (AUC) measuring patients’ adaptation rate,calculated by performing a power fit on the mean learning values of each participant; (iii) the coefficient of variation (CV)measuring the variability of motor performance during the adaptation plateau phase (i.e., when the AUC is stabilized and reaches stable levels) and calculated as the standard deviation (SD) divided by the mean over trials belonging to the plateau phase (AUC/Time-to-target). All these metrics will be represented in ordinal and mean group scores for post vs. pre-tDCS baseline intervention, and for the follow-up milestone and compared across tDCS groups.

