In order to quantify sustained attentional abilities (as a proxy of dorsolateral prefrontal  modulation by tDCS) with the AX-CPT task, we will analyse the total number of errors used as a proxy of sustained attention failure. An ordinal value will be taken and group means will be compared between pre- vs. post-tDCS  and for the follow-up milestone. In order to indentify and quantify changes of visuo-spatial performance (as a proxy of visuo-spatial orienting and selective attentional disability), the number of  crossed/circled letters (letter cancellation test) or bells (Bells cancellation test) and the shift (in mm and % of the total line length) of manual bisections from the precise midpoint of each line (line bisection test) will be analysed. Mean group total ordinal scores will be compared between groups acrossthe different time points (pre-, post-tDCS s and follow-up milestones). Other unanticipated complementary metrics could also be taken into account for the final analyses.

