## Statistical analyses

In order to evaluate the therapeutic potential of each tDCS intervention in post-stroke motor recovery, we will first asses the data distribution of the Fugl-Meyer Assessment by means of Shapiro–Wilk method. In the case of normal distribution, clinical outcomes will be compared using repeated measures analysis of variance (two-way ANOVA) with “TIME” (baseline, post-tDCS, follow-up) as within-subject factor, and “GROUP” (ipsi-DLPFC, contra-CEREB, ipsi-DLPFC + contra-CEREB, SHAM) as between-subject factor. Post hoc pair-wise comparisons will be performed using a Bonferroni correction for multiple comparisons. In the case of non-normal data distribution, a non-parametric Kruskal–Wallis test will replace repeated measures ANOVA. Linear mixed models and Pearson’s (for normally distributed data) or Spearman's correlation coefficients corrected for multiple comparisons between AX-CPT, visuo-motor adaptation task, and the Fugl-Meyer outcomes will be used to explore behavioral correlation between motor, attentional, and cognitive control domains. All data will be presented as mean ± standard deviation and statistical significance will be set for all tests at *p* ≤ 0.05.

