In such context, the protocol *E-Brain* aims at comparing in separate and independent patient groups three active anodal tDCS conditions (ipsi-DLPFC, contra-CEREB, ipsi-DLPFC + contra-CEREB) and a SHAM tDCS intervention. Our design will contribute to identifying the most beneficial strategy comparing single-site (monofocal) or combined (bifocal) dual-site approaches by means of high-density tDCS. The study will also ascertain changes in DLPFC and anterior cerebellar lobe modulation by means of tasks specifically assessing sustained attention/cognitive control and visuo-motor adaptation skills respectively, to verify that upper limb motor improvements are mediated by the modulation of such contributing networks. Moreover, different EEG synchrony measures recorded along the intervention will report on local and “large-scale” modulations of primary motor systems from distant regions, via changes in functional connectivity and local and long-range synchronization mechanisms [67] and reveal the longer-term neuroplastic properties associated with such effects.

Still a key challenge for clinical neuroscience [68, 69], this approach is currently inspiring a transition from conventional “single-site” neuromodulation focused on targeting directly impaired systems, towards multifocal stimulation set-ups with multiple electrical sources able to address more holistically, network dysfunction [70, 71]. Moreover, it is supported for example by recent work demonstrating higher modulatory power on cortical reactivity [66] and changes in corticospinal excitability [72, 73] by dual-site (bifocal) stimulation as compared to single-site (monofocal) tDCS approaches. In this context, our protocol will be among the first fully adopting the notion of post-stroke motor paralysis as a network impairment involving not only motor but also non-motor cognitive systems contributing indirectly to voluntary motion. Under such perspective, we will pursue the modulation of network dysfunction via a circuit-based therapeutic approach and promote local and global synergistic network-wide effects (“reshaping”) between non-purely primary motor regions (such as the prefrontal cortex and the anterior cerebellar lobe) and motor and premotor systems to facilitate motor post-stroke rehabilitation and effective recovery.

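### The Discussion promises to verify mediation, but the plan never ties the arm comparison on the tasks to the task–Fugl-Meyer correlation, which can be significant without any network modulation

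*Protocol article*

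**What the plan says.** - **Claim.** The Discussion says the trial will measure prefrontal and cerebellar modulation with the AX-CPT and visuo-motor tasks, "to verify that upper limb motor improvements are mediated by the modulation of such contributing networks".
- **Analysis joining task and motor scores.** Statistical analyses plans linear mixed models and Pearson or Spearman "correlation coefficients corrected for multiple comparisons between AX-CPT, visuo-motor adaptation task, and the Fugl-Meyer outcomes", which "will be used to explore behavioral correlation between motor, attentional, and cognitive control domains". No adjustment for arm or baseline, and no indirect effect, is stated for it. The other analyses in that section that involve these outcomes relate them to electric-field and EEG measures, and are also framed as correlations.
- **Arm comparison on the tasks.** Analysis of clinical and cognitive performance outcome measures sets out to contrast active stimulation with sham. The visuo-motor metrics are taken before and after treatment and "for the follow-up milestone and compared across tDCS groups". For the AX-CPT, "we will analyse the total number of errors used as a proxy of sustained attention failure".
- **Other sources of improvement.** Sham tDCS condition describes a phase "during which, instances of spontaneous recovery might still operate", says that ongoing rehabilitation could contribute, and wants sham to counter "improvement effects caused by familiarization and training in evaluation tasks performed several times during the study follow-up". Under Associated clinical rehabilitation, patients receive motor therapy, and "neuropsychological rehabilitation is mainly centered on training executive function and the management of emotions". The limitations paragraph of the Discussion adds that rehabilitation could differ somewhat between patients and that motivation and outside activity are not controlled.

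**The concern.** Mediation is a causal chain: stimulation changes attention or adaptation, and that change produces the motor gain. A correlation between task and Fugl-Meyer scores has a different null hypothesis, namely that the two scores are unrelated across patients. Any cause that lifts some patients more than others on both scores will make that null false, with or without stimulation. The article itself names candidates for such a cause and gives them as the reason for the sham arm, yet the correlation is not stated to use the sham contrast.

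The visuo-motor task adds a further ambiguity. It is performed with the paretic limb, the same limb that FMA-UE scores, so a direct motor gain could improve the task with no cerebellar mediation.

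What is at stake is the mechanistic conclusion. The Discussion presents the indirect, cognitive route to motor recovery as the novelty of the trial, and a significant correlation could be read as confirming it.

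**Working it through.** The article states no correlation, effect size or power, so there is no figure to reproduce.

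**Inputs from the article.** N = 60 in four arms of 15, ratio 1:1:1:1 (Sample size; Randomization and blinding); significance at 0.05 (Statistical analyses).

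**Assumptions.** Two-sided tests on change scores, pooled over arms. Four metrics for the multiplicity correction (AX-CPT errors, SumErr, AUC, CV). A shared patient-level correlation ρ of 0.1 to 0.4. Stimulation effects of 0.8 SD where present. Scores are coded so that positive means improvement; AX-CPT errors and SumErr are error scores, so their raw correlation with FMA gain would be negative.

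**Model.** Task change T = √ρ·U + √(1−ρ)·e₁ + task effect; FMA change F = √ρ·U + √(1−ρ)·e₂ + FMA effect. U is the patient's own shared recovery, and e₁ and e₂ are independent.

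**Step 1: no stimulation effect on either score.** Chance of a significant positive correlation ≈ Φ(atanh(ρ)·√(N−3) − z), with √57 = 7.550, z = 1.960 uncorrected and z = 2.498 at 0.05/4. For ρ = 0.2: 0.2027 × 7.550 = 1.531. Then Φ(1.531 − 1.960) = 33%, and Φ(1.531 − 2.498) = 17%.

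| ρ | uncorrected | Bonferroni, 4 |
|---|---|---|
| 0.1 | 11.5% | 4% |
| 0.2 | 33% | 17% |
| 0.3 | 65% | 44% |
| 0.4 | 89% | 76% |

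Simulation (4,000 trials per setting) gives 12%, 34%, 65% and 89% uncorrected.

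**Step 2: task untouched, direct 0.8-SD effect on FMA in the combined arm.** The correlation is significant in about 10%, 32%, 60% and 86% of simulated trials for ρ = 0.1, 0.2, 0.3 and 0.4. With Bonferroni it is about 4%, 15%, 39% and 70%. Repeat runs differ by a point or two.

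**Step 3: what the arm comparison adds.** In the Step 2 setting, an arm-adjusted slope on its own is still significant in 33%, 64% and 89% of trials (ρ = 0.2, 0.3, 0.4). Adjustment alone does not help, and it makes little difference here whether the planned correlation pools arms. Requiring a combined-versus-sham difference on the task as well brings false support down to about 1.4–1.6%, 2.9–3.0% and 4.0–4.8%. The protection comes from the arm contrast, which is already planned.

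**Step 4: what arm adjustment adds.** Suppose stimulation moves both scores by 0.8 SD through separate routes, with ρ = 0. Requiring the task contrast plus an unadjusted correlation gives false support in 9% of trials. With the arm-adjusted slope it is 1.4%, close to the product of the contrast's power and a one-directional 2.5% error: 0.59 × 0.025 = 1.5%.

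**Step 5: limit of the combined rule.** With those separate 0.8-SD effects and shared recovery of ρ = 0.2, 0.3 and 0.4, the rule still fires in 18%, 35% and 50% of trials although nothing is mediated.

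**Step 6: uniform gains.** A practice gain identical in every patient shifts means only: r is about 0, significant and positive in about 2% of runs.

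**Step 7: power of the task contrast.** Φ(d·√(15/2) − 1.960) for one active-versus-sham comparison is 28% at d = 0.5, 59% at d = 0.8 and 78% at d = 1.0.

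**The case against.** The strongest reply is that the correlation is only half the plan. Task scores are also compared between active and sham arms, and the Discussion sentence rests on the tasks, not expressly on the correlation. If stimulation did nothing to the tasks, that comparison would be significant only about 5% of the time. This stands. A reader might infer that the article's only mechanistic test is a correlation, and the text does not support that. What remains is that the arm comparison shows whether stimulation moves the task, not whether the motor gain runs through it, and no rule joins the two results.

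Second, a reader might infer that the article says shared recovery moves all scores in all arms, so that the correlation must be positive. It says only that such recovery might operate, that rehabilitation could contribute and that programmes could differ. The correlation can be positive, for improvement, and only if the gains vary together between patients.

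Third, Study objectives speaks of evaluating, exploring and finding associated biomarkers, and the trial is an exploratory pilot. That is fair, and it makes *verify* the outlier. It also means one cannot assert that a correlation would in fact be reported as verification.

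Fourth, the covariates of the mixed models may be set out in a fuller document. That is possible, but the Discussion's claim would still exceed the exploratory purpose stated for the analysis.

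**Conclusion.** The point holds in this limited form. The Discussion claims verification of mediation. The plan has an arm comparison on the tasks and an exploratory task–FMA correlation, but neither combines them nor states arm or baseline adjustment for the correlation. With stimulation leaving the tasks untouched, the correlation is significant in about 10% to 86% of trials, or 4% to 70% with Bonferroni over four metrics. These ranges rest on an assumed shared correlation of 0.1 to 0.4, an assumed 0.8-SD direct effect on FMA, and change scores pooled over arms. The low end is close to harmless and the high end is not, and the article gives no basis for choosing between them.

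A reader might also infer that an arm-based mediation model would settle the question. Step 5 shows that it would not, so softening the claim is needed whichever model is used. The primary FMA-UE comparison between arms is unaffected.

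**What to change.** 1. In the Discussion, replace the verification claim with exploring whether the results are consistent with mediation.
2. In Statistical analyses, regress FMA-UE change on task change with GROUP and the baseline scores in the model. Report the indirect effect with a bootstrap interval, and the sham-arm association as a benchmark.
3. Describe results as consistent with mediation only if the active-versus-sham task effect, already planned, and the arm-adjusted slope both hold.
4. Label this analysis exploratory, noting that shared recovery can still confound the slope when stimulation affects both scores by independent routes. Label unadjusted correlations as association only.

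No new data are needed. The cost is a little more modelling and a more modest mechanistic claim, which will be harder to reach with 15 patients per arm.

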## Trial status

The first version of the study protocol was approved by the local ethics committee at the Institut d’Investigació Sanitària Pere Virgili (IISPV, Tarragona, Spain) on July 9th 2021. A pilot group of *n* = 8 patients, which will not be included in the final analyses served to pilot the initial version of the protocol, hence to improve its design and content, and to test the adequacy, feasibility, and reliability of some of the assessment tasks, leading to the current final version. Participant recruitment began on March 2022; and since then, *n* = 11 participants have successfully completed the protocol. Participant recruitment is planned to be completed by end of December 2025.

## Data Availability

Not applicable. No data is available at this point because authors are still in the process of gathering such.

## Abbreviations

AX-CPT: AX continuous performance task
BA: Brodmann area
CAT12: Computational anatomy toolbox 12
CEREB: Cerebellum
CNS: Central nervous system
Coords: Coordinates
CSF: Cerebrospinal fluid
contra-CEREB: Contralesional cerebellar stimulation
CT: Computed tomography
DAN: Dorsal attention network
DTI: Diffusion tensor imaging
DLPFC: Dorsolateral prefrontal cortex
EEG: Electroencephalography
E-field: Electric field
FMA: Fugl-Meyer assessment
fMRI: Functional magnetic resonance image
GM: Gray Matter
HD-tDCS: High-density transcranial direct current stimulation
Hz: Hertz
ipsi-DLPFC: Ipsilesional dorsolateral prefrontal cortex
mA: Milliamps
MCA: Middle cerebral artery
MNI: Montreal Neurological Institute
MoCA: Montreal cognitive assessment
MRI: Magnetic resonance imaging
NIBS: Non-invasive brain stimulation
NIHSS: National institute of health stroke scale
BSIdir: Pair-wise derived brain symmetry index
PET: Positron emission tomography
PSD: Power spectrum density
ROIs: Regions of interest
SMN: Sensory-motor network
SPM12: Statistical parametric mapping
tDCS: Transcranial direct current stimulation
tES: Transcranial electric stimulation
V/m: Volts per meter
W: Week
WM: White Matter
|E|: Electric field strength
|nE|: Normal component of the electric field
